## Abstract

**Background:**

Penetrating keratoplasty can commonly restore vision in corneal blindness. However, immunological graft reactions may induce irreversible graft failure in a substantial percentage. Repeat keratoplasties in turn are associated with increased risk of graft failure and possibly irreversible blindness. Topical as well as systemic immunosuppressants are administered for prophylaxis. However, severe adverse effects limit long-term usage. By contrast, matching for transplantation antigens might be effective for a long time.

**Methods:**

FANCY is a prospective, controlled, randomised, double-blind, multi-centre clinical trial with two parallel arms. The primary objective is to evaluate superiority of the proposed HLA matching strategy in comparison to random graft assignment with respect to the primary endpoint ‘time to first endothelial graft rejection’. Relevant inclusion criteria are age over 18 years and waiting for penetrating or endothelial lamellar keratoplasty. The most important exclusion criteria are abuse of medication and/or drugs and an anticipated waiting time for an HLA match longer than 6 months. After randomisation, patients either receive a HLA-matched graft (experimental intervention) or a random graft (control intervention). The calculated sample size is 620 patients. The trial started in 2009 with a recruitment period of 24 months. A total of 654 patients were included during this time.

**Discussion:**

The primary goal of FANCY is to assess whether histocompatibility matching is feasible and effective in the broad clinical routine. However, during the course of the trial, the landscape of keratoplasty changed due to the rise of Descemet Membrane Endothelial Keratoplasty (DMEK). Nowadays, immune reactions are confined mostly to the ‘high-risk’ subgroups. If we would design FANCY in 2014, we would narrow down the inclusion criteria to include only the high risk patients and accept longer waiting times for a matching donor here.

**Trial registration:**

The unique identifying number of the FANCY trial is NCT00810472.

## Background

### Graft rejection after keratoplasty

Corneal diseases are among the five most common causes of blindness. FANCY was designed back in 2007. At that time, penetrating keratoplasty was the undisputed gold standard for corneal transplantation. This procedure can restore vision in the majority of affected patients due to the ocular immune privilege. Nevertheless, immunological graft reactions are a major barrier towards long-term success. They give either rise to irreversible graft failure immediately or at least promote late graft failure from endothelial cell loss. Penetrating repeat keratoplasties due to immunological graft failures are considered at high immunological risk irrespective of primary indication. This predicament commonly initiates a vicious cycle in affected patients due to increased risk of rejections in consecutive repeat keratoplasties.

### Current strategies of secondary prophylaxis

Immune reactions cannot currently be sufficiently prevented in the postoperative course of penetrating keratoplasty: on average, 18% in normal-risk penetrating keratoplasty and 75% of high-risk cases are affected - despite standard medical prophylaxis from topical steroids and in most high-risk situations additional systemic immunosuppression. These regimens have to be discontinued at some point in time due to the accumulating risk of severe adverse drug reactions: topical steroids commonly induce complications such as cataract or glaucoma. Systemic immunosuppressants like Cyclosporine A or Mycophenolate Mofetil may be effective from pilot studies [1] but have the potential to induce kidney failure as well as malignancies in the long run. Furthermore, this approach is hampered by the off-label mode of prescription and malcompliance.

### Considerations on primary prophylaxis

We are aware of no data on the molecular mechanisms of allorecognition of the corneal graft in the human situation. However, autologous grafts (such as in auto rotational keratoplasty) are never rejected. Both in-vitro and in-vivo data point towards a central role of the HLA system in eliciting immune reactions. For this reason, a reduction of the antigenic load in the graft by means of matching for HLA and most likely also of further (’minor’, H) transplantation antigens has a strong potential to reduce the risk of graft rejections.

## Methods/design

The trial is funded by the Deutsche Forschungsgemeinschaft (DFG). The study received appropriate ethics committees approval from the central ethics committee (University of Freiburg, 229/07) and the local ethics committees (University of Erlangen-Nuremberg, 4093-CH; University of Duisburg-Essen, 09–4134; University of Frankfurt, 234/09; Medical Association of Hamburg, MC-239/09; Medical Association of Saarland, 134/09; University of Kiel, B 255/09; Medical Association of Rheinland-Pfalz, 837.343.09 (6849); Ludwig-Maximilian-University of Munich, 294–09; University of Muenster, 2009-347-b-S; University of Wuerzburg, 31/10). Being registered at clinicaltrials.gov the unique identifying number of the FANCY trial is http://NCT00810472. Patient’s written consent was obtained prior to any study-specific procedures.

### Trial design

This is a prospective, controlled, randomised, double-blind multi-centre clinical trial with two parallel groups. The intervention is HLA matching for HLA-A, -B and -DRB1. Donors with less than 3 HLA mismatches are considered HLA matched. In the matching arm, the first donor exerting a 4/6 match (or “better“) is accepted within the first three months. A differential matching strategy on the basis of HLA-Matchmaker is additionally activated thereafter. The next available graft is assigned after 6 months. In the control arm, the next available donor is assigned. The matching arm is prioritised when a single graft could be allocated to more than one recipient.

### Objectives

The primary objective of the study is to demonstrate superiority of the proposed HLA matching strategy in comparison to random graft assignment with respect to the endpoint ‘time from keratoplasty to first endothelial graft rejection’ in penetrating keratoplasty. Secondary objectives of the study are: assessment of safety and tolerability; evaluation of time on waiting list and matching failures (failure to allocate a matching donor in the HLA matching arm within 6 months); retrospective analyses of the number and nature of mismatched antigens (HLA and minor transplantation antigens) in the patients with immune reactions; Retrospective analyses on the extent of antibody production against HLA mismatches in the rejecting patients.

### Setting

A multi-centre study design was chosen to account for patient recruitment with a reasonable time frame, for inclusion of a wider range of patients increasing the generalisability of the results and for the dissemination of findings when they become available. Trial sites are located in Erlangen, Essen, Frankfurt, Freiburg, Hamburg, Homburg/Saar, Kiel, Mainz, Munich, Muenster and Wuerzburg.

### Population

The target population of this trial is waiting for penetrating keratoplasty or lamellar endothelial keratoplasty. The majority of all indications for corneal transplantation are eligible for inclusion.

### Inclusion criteria

General inclusion criteria are: (1) patient’s written informed consent has been obtained, (2) 18 years or older at time of informed consent, (3) patient is awaiting either penetrating or endothelial lamellar keratoplasty. Indication-specific inclusion criteria are all corneal conditions that warrant either penetrating or lamellar endothelial keratoplasty.

### Exclusion criteria

General exclusion criteria are: (1) patient without legal capacity who is unable to understand the nature, significance and consequences of the study, (2) simultaneous participation in other interventional trials which could interfere with this trial and/or participation before the end of a required restriction period, (3) participation in a clinical trial within the last thirty days before the start of this study, (4) previous participation (randomisation) in this study, (5) known or persistent abuse of medication and/or drugs (such as alcohol), (6) persons who are in a relationship of dependence/employment with the sponsor or the investigator. An indication-specific exclusion criterion is predicted waiting time for a 4/6 HLA match greater than 6 months. The computation is performed by the trial software system on the basis of the patient's HLA phenotype and the HLA frequencies in the donor pool.

### Treatment arms

All randomised trial patients on the waiting lists are matched against the donor-pool on a continuous basis. See Figure 1 for an overview of the underlying allocation algorithm. The matching arm is always prioritised: grafts are routed into the random arm when there is no match in the matching arm at time of allocation. Each patient in the matching arm is assigned a random graft after 6 months. The investigators are notified via email when a graft has been assigned to a trial patient. Whenever a keratoplasty is not possible on this basis, the investigator has to inform the trial coordinator as soon as possible (see the trial software manual). The waiting time limitation of 6 months in the matching arm is reset in this case.

**Figure 1 Fig1:**
[figure not shown]
**Schematic of the allocation algorithm.** The matching arm is prioritised: the random arm is only assigned grafts that are not applicable to the matching arm at time of allocation.

### Visit schedule

We schedule a total of four follow up visits over a time span of two years post operatively (see Table 1). At each visit we ask for assessment of graft clarity and adverse events. We also demand careful recording of all concomitant medications.

**Table 1 Tab1:** **Visit schedule**

Assessment	Screening	Preoperative visit	Keratoplasty	Visit 1	Visit 2	Visit 3	Close-out
Months/weeks after keratoplasty	Variable timeslot/within 6 month before keratoplasty	-1 week	= 0	4 (±3 weeks)	12 (±3 weeks)	18 (±3 weeks)	24 (±6 weeks)
Informed consent	x						
HLA typing	x						
Check eligibility	x						
Randomisation	x						
Demographic data	x	(x)*	(x)*				
Classification into high vs. low-risk patients	x	(x)*	(x)*				
Concomitant medications	x	(x)*		x	x	x	x
Endothelial cell density				x	x	x	x
Details on suturing		x	(x)*				
Details on trephination		x	(x)*				
Slit lamp evaluation of graft				x	x	x	x
Adverse events	x						
Post-OP complications in the study eye				x	x	x	x

*if data were not requested before.

The postoperative treatment and medical aftercare in corneal transplantation is recommended by the ’Sektion Kornea’ of the German Ophthalmologic Society (’Deutsche Ophthalmologische Gesellschaft’) in both study arms. Treatment of graft rejections is at the discretion of the investigator and may include topical, intracameral and systemic steroids.

### Outcome measures

The primary endpoint is the time interval from keratoplasty to the first graft rejection. Graft rejections are defined by either newly diagnosed keratic precipitates or rejection line in the donor endothelium, subepithelial infiltrates not explained by a preceding adenoviral conjunctivitis or newly diagnosed global graft edema that is otherwise not explained. The date of graft rejection is defined as the date on which treatment of the rejection is initiated. If no treatment was initiated, then the time of first mention of the rejection in the medical record is defined as date of the rejection.

Secondary endpoints are: (1) Number of HLA mismatches per patient in the matching arm, (2) number and nature of mismatched HLA/H transplantation antigens in the rejecting patients, (3) percentage of annual endothelial cell loss by means of exponential regression parameters [2, 3], (4) referring to substudy: ratio of HLA-antibody titers in blood samples after graft rejection to the respective titers prior to keratoplasty.

### Sample size

The sample size calculation is based on the primary endpoint ‘time to first endothelial graft rejection’. A rejection rate of 30% after 2 years is expected in the control group, and a reduction of events by 30% is considered to be clinically relevant, corresponding to a rejection rate of 21% after 2 years in the HLA matched group and a hazard ratio of 1.51. In order to detect this difference with a power of 80% at a 2-sided significance level of alpha = 5%, a total of 184 events is required. In order to account for the expected 10% match failures because of the intention-to-treat principle (see below), we randomly generated 1000 datasets, each with the proposed sample size of 620 and the expected matching effect of 30% after 3 years against a background of 30% immune reactions. After introducing 10% matching failures in each of these datasets, the mean matching effect dropped from 30% to 27%. These results in an assumed rejection rate of 21.9% in the HLA matched group (instead of 21% without any matching failures) and a hazard ratio of 1.44 (instead of 1.51). With an accrual period of 1.5 years for and a reference time of 1.5 years (almost all immune reactions have already occurred at this postoperative point in time), the power of the intention to treat analysis is 83%.

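### The stated 83% power does not follow from the plan's own rates: 620 patients followed for two years give about 161 events and about 64% power

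*Protocol article*

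**What the plan says.** All the sample-size inputs are in the Sample size section of the protocol article. It starts from the control arm: "A rejection rate of 30% after 2 years is expected in the control group". The target effect is a 30% relative reduction, "corresponding to a rejection rate of 21% after 2 years in the HLA matched group and a hazard ratio of 1.51". The event target is set "with a power of 80% at a 2-sided significance level of alpha = 5" per cent, and the section concludes that "a total of 184 events is required".

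It then allows for 10% match failures by simulating datasets of 620 patients with an "expected matching effect of 30% after 3 years against a background of 30% immune reactions". The diluted effect is "an assumed rejection rate of 21.9% in the HLA matched group" and a hazard ratio of 1.44. With 1.5 years of accrual and a reference time of 1.5 years, by which almost all reactions are said to have occurred, the section states that "the power of the intention to treat analysis is 83" per cent. It gives no expected number of events for 620 patients.

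The Visit schedule section plans "a total of four follow up visits over a time span of two years post operatively". Table 1 places the close-out visit at 24 months (±6 weeks).

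**The concern.** A weaker effect needs more events. Moving from a hazard ratio of 1.51 to 1.44 raises the requirement well above 184, and 620 patients at the stated two-year rates do not reach even 184. The time base is also unclear. The 30% rate is a two-year figure in one sentence and sits beside a three-year horizon in the next, and the power statement uses a 1.5-year reference time whose meaning is not explained.

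The power claim for the primary analysis governs how a non-significant result is read. At 83% power, the chance of missing the target effect is about one in six. At 64% it is more than one in three. A reader who trusts the 83% would give a null result more weight against HLA matching than the design supports.

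**Working it through.** **Inputs** (Sample size section unless noted): two-sided alpha 5%; control rate 30% at 2 years; matched-arm rate 21%, or 21.9% after dilution; N = 620, so 310 per arm at 1:1 (Randomisation and blinding); follow-up of 24 months (Visit schedule, Table 1); 654 recruited (Study progress).

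**Formulas** (proportional hazards, 1:1 allocation, Schoenfeld):
- HR = ln(1 − control rate) / ln(1 − matched rate)
- Events needed = 4(z₁₋α/₂ + z_power)² / (ln HR)²
- Power = Φ(√events/2 × ln HR − 1.96)

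**Step 1. What reproduces.**
- Undiluted HR = ln 0.70 / ln 0.79 = 1.513 (stated 1.51).
- Events for 80% power = 4(1.96 + 0.8416)² / 0.4142² = 183, or 185 with HR rounded to 1.51 (stated 184).
- Diluted rate = 0.9 × 21% + 0.1 × 30% = 21.9% (as stated).
- Diluted HR = ln 0.70 / ln 0.781 = 1.443 (stated 1.44).

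**Step 2. Events needed at the diluted effect** (ln HR = 0.3667): 233 for 80% power and 253 for 83%. As a share of the sample, 253/620 = 41%. The plan's pooled two-year rate is (30% + 21.9%)/2 = 25.95%.

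**Step 3. Events expected and the resulting power.**

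| Case | Events | Power |
|---|---|---|
| 620, undiluted (30% vs 21%) | 310 × 0.51 = 158 | 74% |
| 620, diluted (30% vs 21.9%) | 310 × 0.519 = 160.9 | 64% |
| 654, diluted | 327 × 0.519 = 169.7 | 67% |
| 184 events reached, diluted HR | 184 | 70% |

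For the second row: √160.9/2 × 0.3667 − 1.96 = 0.366, and Φ(0.366) = 0.643. Freedman's formula gives 63.3%, a comparison of two proportions 63.4%, and simulated log-rank tests 64.1% (20,000 runs, fixed two-year follow-up).

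Holding 83% would take 253/0.2595, about 973 patients with complete two-year follow-up.

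**Step 4. Other readings of the time base**, all with 620 patients, the diluted HR, constant hazards and a two-sided 5% test.

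| Reading | Events | Power |
|---|---|---|
| Rates at 2 years; 1.5 years accrual; 1.5 years minimum follow-up; no 24-month cap | 177 | 68% |
| Rates at 1.5 years; everyone followed to 24 months | 204 | 75% |
| Rates at 1.5 years; 1.5 years accrual; 1.5 years minimum follow-up; no cap | 223 | 78% |
| Rates at 2 years; everyone followed for 3.5 years | 253 | 83% |
| Rates at 1.5 years; 1.5 years accrual; 2 years minimum follow-up (2 to 3.5 years each); no cap | 260 | 84% (Freedman 83%) |

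Only the last two reach the stated figure. Both need follow-up well past the close-out visit, and both need reactions to continue at the same rate after the time by which the plan says almost all have occurred.

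**Step 5. Patients not transplanted.** The Statistical analysis section excludes them, and the Sample size section states no allowance for it. The article gives no rate, so a range is assumed here: excluding 5%, 10% or 20% of 620 leaves 152.9, 144.8 or 128.7 events and 62%, 60% or 55% power. Excluding about 5% of the 654 recruited (654 × 0.95 = 621) brings the trial back to about 64%.

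**The case against.** The strongest reply is that 83% may be correct arithmetic on inputs other than the published ones. The last row of the second table above comes close to the section's own timings, and the original calculation could have been run that way. The 80% and the 83% also need not move together, since the first defines an event target and the second is the power of a fixed sample under an accrual model. With about 260 events, 83% at a hazard ratio of 1.44 is coherent. This stands as an explanation of where the number may have come from. It does not rescue the number, because the inputs it needs conflict with the two-year rates, the 24-month close-out and the remark on event timing.

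A second reply is that 64% is one end of a range. If the reference time of 1.5 years is the time to which the 30% and 21.9% apply, and the hazard then stays constant to 24 months, power is about 75%. That is fair, and the correction should acknowledge it. The plan attaches the rates explicitly to two years, however, and if almost all reactions occur by 1.5 years the extra half year adds little. Both points favour 64%.

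Finally, a hazard ratio with a 95% confidence interval is already planned, as is adjustment for prognostic factors. The interval does help interpretation. The effect of adjustment on power is not quantified in the article, so it cannot be credited with closing the gap.

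**Conclusion.** The stated 83% is wrong as written. On the plan's explicit two-year rates and two-year follow-up, 620 patients give about 161 events and about 64% power at the diluted hazard ratio, and the 654 recruited give about 67%. The reading most favourable to the plan that still respects the 24-month close-out gives about 75%. The plan's own target of 184 events is not expected either, with or without dilution.

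These figures assume proportional hazards, 1:1 allocation, complete two-year follow-up and transplantation of every randomised patient. Loss to follow-up and exclusion of untransplanted patients would lower them. The fault lies in inputs that contradict one another within the section and with the visit schedule, whether or not the original software run was arithmetically correct.

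**What to change.** Revise the Sample size section, and carry the same figures into the analysis plan and the final report:

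- Use one horizon, two years, for the 30%, 21% and 21.9% rates. Remove the three-year reference, and either explain or drop the 1.5-year reference time.
- State that about 161 events are expected from 620 patients at the diluted effect, fewer than 184.
- Replace 83% with about 64% for 620 patients and about 67% for 654, before any loss to non-transplantation. If the 1.5-year reading was intended, say so, justify the hazard after 1.5 years, and give about 75%.
- Give the effect detectable with 80% power: HR = exp(2 × 2.8016/√160.9) = 1.56, or 30% against 1 − 0.70^(1/1.555) = 20.5%. This is slightly optimistic, because at 20.5% the events fall to 310 × 0.505 = 157.
- State that a non-significant result does not by itself exclude a reduction of 27% to 30%, and that interpretation will rest on the confidence interval already planned.

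The cost is a rewording and a less favourable stated power. No extra patients are needed, and the randomisation and primary analysis stay as they are.

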### Randomisation and blinding

Randomisation is performed, stratified by centre, in blocks of variable length. An equal distribution between treatment arms (ratio of 1:1) will be striven for. The randomisation list is generated by the Department of Biometry and Data Management of the Clinical Trial Unit, Medical Center – University of Freiburg.

The electronic version of the randomisation list was integrated in the trial software. Treatment assignment was thus performed via the trial software. In our study, this was the best possible way of blinding.

### Statistical analysis

The primary analysis of this clinical trial will be conducted according to the intention-to-treat (ITT) principle. This means that the patients will be analysed in the treatment arms to which they were randomised, irrespective of whether they refused or discontinued the treatment or whether other protocol violations are revealed. Patients not receiving keratoplasty cannot contribute any information to the analysis of treatment efficacy and will therefore be excluded from the ITT population.

The primary endpoint ‘time to first graft rejection’ will be analysed with a Cox proportional hazards model. The hazard ratio comparing control and treatment group will be estimated and tested within this model. The 2-sided 95% confidence interval will also be calculated. The Cox model will be stratified by study centre. We plan to include the recognised prognostic factors on immune reactions against the graft and overall graft survival in the model. Details will be fixed at the latest in a statistical analysis plan to be prepared prior to the analysis. The analysis of secondary endpoints ‘number of mismatches (HLA, H)’ will be performed descriptively, i.e. mean, median, range, standard deviation, and percentiles will be given. ‘Time on the waiting list’ will be estimated using the Kaplan Meier method separately in each treatment group, where patients not receiving keratoplasty are considered as censored observations.

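### The Kaplan-Meier estimate of waiting time censors patients who leave the list, so in either arm it overstates the proportion transplanted (minor; descriptive secondary objective)

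*Protocol article*

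**What the plan says.** The Objectives section of the protocol article lists among the secondary objectives "evaluation of time on waiting list and matching failures (failure to allocate a matching donor in the HLA matching arm within 6 months"). The Statistical analysis section then fixes the method: "Time on the waiting list’ will be estimated using the Kaplan Meier method separately in each treatment group". The same sentence goes on to settle how patients who never get a trial graft are handled: "where patients not receiving keratoplasty are considered as censored observations". No distinction is made by reason for not being transplanted, and no competing-risk method is named.

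Three other statements bear on the point:

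- The same section removes these patients from the efficacy analysis: "Patients not receiving keratoplasty cannot contribute any information to the analysis of treatment efficacy and will therefore be excluded from the ITT population".
- The Treatment arms section sets a fallback: "Each patient in the matching arm is assigned a random graft after 6 months". If keratoplasty on an assigned graft is not possible, "The waiting time limitation of 6 months in the matching arm is reset in this case".
- The control arm is second in line: "grafts are routed into the random arm when there is no match in the matching arm at time of allocation".

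**The concern.** Two kinds of patient end without a trial keratoplasty. Some are still waiting when the data are cut; their waiting time is incomplete, and censoring is right for them. Others have died, withdrawn or been grafted elsewhere, and can no longer receive the trial graft. Censoring the second kind treats them as if they remained candidates with the same prospects as those still listed. One minus Kaplan-Meier then answers a hypothetical question (what proportion would have been grafted by time t if nobody ever left), not the factual one (what proportion of randomised patients had been grafted by time t).

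Waiting is the price of a matching strategy, and the Discussion describes the trial's goal partly in terms of feasibility within a reasonable time. A reader will take the waiting-time curve as the proportion transplanted. If many patients leave while waiting, that reading is too favourable.

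**Working it through.** **Figures in the document.** The article states no waiting-time distribution, no exit rate and no number never transplanted, so there is no figure of its own to reproduce. The nearest number, the 10% match failures in Sample size, concerns patients without a match. They can still receive a graft, so it is not an exit rate.

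**Direction.** This needs no assumption about size. When some patients leave before keratoplasty, one minus Kaplan-Meier with leavers censored is never below the Aalen-Johansen cumulative incidence and exceeds it at any later time when grafts are still being given.

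**Size, illustration 1.** All inputs are assumptions:

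- median wait m = 2, 3 or 4 months if nobody left;
- eventual share leaving q = 5%, 10% or 20%;
- constant hazards.

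Formulas:

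- graft hazard λ = ln 2 / m; exit hazard μ = λq/(1 − q)
- 1 − KM(t) = 1 − exp(−λt)
- cumulative incidence CI(t) = [λ/(λ+μ)] × [1 − exp(−(λ+μ)t)]
- median of CI = −ln(1 − 0.5/(1 − q)) / (λ+μ)

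Example, m = 3 and q = 10%: λ = 0.2310 and μ = 0.0257 per month. At 6 months 1 − KM = 75.0% and CI = 0.9 × (1 − exp(−0.2567 × 6)) = 70.7%, an excess of 4.3 points.

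| m (months) | q | 1−KM at 6 mo | CI at 6 mo | Excess (points) | Time at which CI reaches 50% (months) |
|---|---|---|---|---|---|
| 2 | 5% | 87.5% | 84.4% | 3.1 | 2.05 |
| 2 | 10% | 87.5% | 81.1% | 6.4 | 2.11 |
| 2 | 20% | 87.5% | 74.1% | 13.4 | 2.26 |
| 3 | 5% | 75.0% | 72.9% | 2.1 | 3.07 |
| 3 | 10% | 75.0% | 70.7% | 4.3 | 3.16 |
| 3 | 20% | 75.0% | 65.9% | 9.1 | 3.40 |
| 4 | 5% | 64.6% | 63.2% | 1.4 | 4.10 |
| 4 | 10% | 64.6% | 61.7% | 3.0 | 4.21 |
| 4 | 20% | 64.6% | 58.2% | 6.5 | 4.53 |

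(Excess is taken from unrounded values.) At 12 months the excess is 3.1–4.6, 6.4–9.3 and 13.4–18.9 points for q = 5%, 10% and 20%.

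**Effect of the 6-month fallback.** If every matching-arm patient still waiting at 6 months were grafted at once, 1 − KM would reach 100%. The share never grafted would be [μ/(λ+μ)] × [1 − exp(−6(λ+μ))], which is 3.3–4.4%, 6.9–9.0% and 14.5–18.5% for the three values of q. This is a limiting case, because the reset of the 6-month limit allows longer waits.

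**Size, illustration 2.** Take λ = 0.384 per month, chosen because exp(−0.384 × 6) = 10.0% matches the protocol's expected match failures. Exit hazards are again assumed.

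- μ = 0.045: at 3 months 1 − KM = 68.4%, CI = (0.384/0.429) × (1 − exp(−1.287)) = 64.8%. Leaving by 6 months: 9.7%. The median moves from 1.81 to 1.91 months.
- μ = 0.10: at 3 months 68.4% against 60.8%. Leaving by 6 months: 19.5%. The median moves from 1.81 to 2.06 months.

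**Between the arms.** In a control arm without a fallback, the eventual excess is μ/(λ+μ). With μ = 0.045 and a mean control wait of about 10 days (λ ≈ 3 per month) it is 1.5 points. With a mean of 1 month it is 0.045/1.045 = 4.3 points, and with 2 months 0.045/0.545 = 8.3 points. The last is close to the 9.7 points in the matching arm. The article gives no control waiting time, so the difference in bias between arms is not determined.

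**The case against.** The strongest reply is that Kaplan-Meier answers a legitimate question. If leaving is unrelated to the prospect of a graft, as both illustrations assume, it correctly estimates how long allocation makes a patient wait while listed. The gaps above are then differences between two quantities, and the stated objective is "evaluation of time on waiting list and matching failures", not the probability of ever being grafted. The median, the usual summary, shifts little: by at most 0.10 months at 5% leaving, 0.21 at 10% and 0.53 at 20%. This stands as a reason to keep Kaplan-Meier as a supplementary display. It does not make the curve a valid proportion transplanted.

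Three stronger conclusions that a reader might draw are not supported:

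- *That the plan conceals how many patients in the matching arm never get a graft.* Patients without keratoplasty must be identified to exclude them from the ITT population, and the number censored is available from a Kaplan-Meier analysis. The article does not say they will go unreported, and a full report may well tabulate them. What holds is narrower: the curve itself cannot show the share, and a bare censored count mixes leavers with those still waiting.
- *That this is a matching-arm problem, or that matching failures are the patients lost.* The rule applies to both arms, and a matching failure is followed by a random graft.
- *That nearly all the error falls on the comparison of arms and flatters matching.* That needs a very short control wait, about 10 days at the assumed exit hazard. It is undocumented and sits badly with control patients being second in line.

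Nor does the article say that measured waiting time restarts after a failed allocation; only the 6-month allocation limit is reset.

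Finally, only a condensed article is shown, and an analysis plan may add detail. The point is nevertheless about a rule the article states, not about one it leaves out.

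**Conclusion.** The concern holds as a minor one. The stated rule handles a competing event as ordinary censoring. One minus Kaplan-Meier therefore overstates the proportion transplanted by a given time in either arm, and the curve cannot show the share never grafted. The bias differs between arms only if waits or exit rates differ.

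The direction is certain once any patients leave before keratoplasty; the size is not known. It rests on assumed exit shares, assumed median waits and constant hazards: negligible if few leave, and above 10 points at 6 months only with about a fifth leaving and short waits. Waiting time is a descriptive secondary objective here, and the primary Cox analysis is not touched by this choice.

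**What to change.** Replace the censoring sentence with a rule along these lines: the cumulative incidence of keratoplasty, measured from randomisation, is estimated in each arm by the Aalen-Johansen method, with leaving the list without keratoplasty (death, withdrawal, graft outside the trial) as the competing event; only patients still waiting at data cut-off are censored. Report both incidences by arm, with counts of non-transplanted patients by reason. Keep Kaplan-Meier, if wanted, as a supplementary display labelled as waiting time while listed.

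The cost is one sentence and a standard routine. The dates of leaving are already needed for the planned censoring. The estimator additionally needs only whether each patient had left or was still waiting, and the counts by reason need the reason for exit. The downside is slightly more analysis work and a slightly less favourable proportion transplanted.
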